### Justification of the study design

This clinical trial is designed to assess the efficacy of an individual cognitive and behavioral therapy in patients with schizophrenia by comparing results from the ENERGY intervention to TAU.

We chose a single blind study to ensure that the psychologist performing the evaluations will be blinded to the randomization arm. It is not possible for patients following the ENERGY intervention to be in a blinded condition.

For the comparison group, called “treatment as usual” (TAU), no definition of classical usual care for patients with schizophrenia exists; the only consensus is that antipsychotic medication is essential [20, 21]. Furthermore, French data show a high rate of care in day hospitals for patients suffering from schizophrenia, with day hospital care accounting for 40% of outpatient care [22]; 84% of French sectors have at least 1 day hospital [23]. So, the TAU could be defined by antipsychotic medication coupled with day hospital care.

### Intervention description

#### Experimental group

Treatment as usual (see below)ENERGY intervention:
Fourteen sessions of 1-h CBT interventionOne session per weekWith a psychologist (different to the psychologist who will perform the assessments)Individual sessions

ENERGY intervention is a cognitive-behavioral intervention developed by Knoop and Bleijenberg [24] and adapted in French by Cantin and colleagues [25]. The ENERGY intervention will be delivered according to a standardized treatment manual comprising six modules addressing fatigue and sleep over 14 individual therapy sessions (Table 1). The treatment encompasses the core CBT principles of psycho-education, behavioral activation, behavioral experiments, cognitive restructuring, problem-solving, and relapse prevention [26]. Sessions will follow the traditional CBT structure of agenda setting, review of homework tasks, and introduction of a new concept/technique with collaborative discussion on how to implement such strategies in the participant’s day-to-day environment [26].

**Table 1 Tab1:** Treatment modules and therapeutic aims

Module	Content summary	Aims
1	Psychoeducation CBT Framework	Shift unhelpful beliefs around symptoms Encourage understanding of link between activity levels and sleep habits with syndrome maintenance
2	Reorganize daily schedules	Initiate pacing of tasks, with optimal number of rest breaks Increase hygiene practices
3	Energy conservation	Integrate meaningful activities depending on goals and available energy
4	Cognitive restructuring Sleep interventions	Modify rest and sleep appraisals Stimulus control, bedtime restriction, hypersomnia management Relaxation
5	Strategies for physical and mental fatigue	Environmental modification, restructuring tasks Cognitive strategies for information processing, attention and time pressure management
6	Review techniques Relapse prevention	Consolidate treatment gains

The CBT framework for addressing fatigue and sleep disturbance was adapted from previous treatment manuals for Chronic Fatigue Syndrome and insomnia, with further modifications made to its content and delivery [27, 28]. To account for possible cognitive impairments frequently encountered in schizophrenia, a specific focus was made on implementing cognitive strategies (e.g., preventing information overload, memory aids, time-pressure management), specific napping schedules, and re-organizing activity levels as a means of energy conservation in addition to pacing and graded activity exposure. Deficits in memory and executive functioning are common in individuals with schizophrenia and may be further exacerbated by poor sleep and persisting fatigue. Relative to conventional CBT, greater structure was imposed in sessions with concrete principles as well as more directive guidance from therapists in problem-solving and generating alternative helpful thoughts. Simplified hand-outs with pictorial cues were provided after each session to minimize information overload and demands on memory. External aids such as diaries and reminders were used to prompt participants to complete prescribed tasks across the week.

#### Control group

Treatment as usual comprises antipsychotic medication, day hospital, and ambulatory care during all the study.

Concomitant care: no concomitant care is prohibited during the trial.

### Outcome measures

We will use a majority of French validated scales and cognitive tests, designed for and commonly used in schizophrenia patients.

#### Primary outcome measures

The primary outcome measure is the score at the Multidimensional Fatigue Inventory (MFI) [29]. The MFI is a self-assessment instrument with 20 items including 5 dimensions: General, Physical, and Mental Fatigue; Reduced Motivation; and Reduced Activity. It was validated in 93 patients with schizophrenia spectrum disorders. The test–retest showed a correlation between .66 and .91 for all subscales of MFI. The internal consistency was .92. The analysis of convergent construct validity showed a correlation of .68 (time 1) and .77 (time 2). No item was systematically identified as being difficult to answer [30].

#### Secondary outcomes measures

Secondary outcome measures will include global functioning, symptomatology, sleep, cognitive functioning, and antipsychotic medication, as well as blood samples:

##### Symptomatology

Positive and Negative Syndrome Scale (PANSS) [31]: The PANSS is a 30-item scale designed to note specific symptomatology of psychotic disorders from 1 to 7. The results include a positive, negative, general psychopathology, and total score allowing categorical and dimensional quotation. The 5 dimensions of this scale were validated in French [32].

Clinical Assessment Interview for Negative symptoms (CAINS) [33]: The Clinical Assessment Interview for Negative Symptoms (CAINS) was developed through a multistage scale development process to measure current level of severity of negative symptoms in individuals with schizophrenia and schizoaffective disorder. The time frame for the ratings is the previous week. The scale was designed for use in treatment trials, but it can also be used in other types of negative symptom research.

The CAINS comprises two subscales: the nine-item Motivation and Pleasure scale and the four-item Expression scale. A composite of the two subscales can be computed.

All ratings are based on a semi-structured interview with prompts and queries. Items are rated on a 5-point (0–4) scale, ranging from 0 (absence of symptom) to 4 (severe symptom level). It should be noted that lower “impaired” scores on several of the items might be within the range of normal variation in the general population. All ratings should be made based solely on descriptors in the anchors without attempting to compare them to clinical or non-clinical reference groups. French validation is in progress by our team with author permission.

Calgary Depression Scale for Schizophrenia (CDSS) [34]: the CDSS is an easy and quick 9-items scale, designed specifically to evaluate depression in schizophrenic patients. The scale was derived from two existing scales by factor analysis and reliability analysis. It has been further tested in two samples. In the first, it has been shown to be reliable, congruent with a self-report scale, and valid. In the second sample, it has been shown that there is no overlap with negative or extrapyramidal symptoms [34]. THE CDSS has been validated in French [35].

##### Sleep

Berlin Questionnaire (BQ) [36]: The questionnaire consists of 3 categories related to the risk of having sleep apnea. The BQ incorporates questions about snoring (section 1), daytime somnolence (section 2), and hypertension and BMI (section 3). In the first section, the participants are asked to score their snoring. In the second section, daytime fatigue and sleepiness during daily activities are investigated, and in the last section, medical history, demographic, and anthropometric measures, such as height and weight, can be evaluated. The first two sections are assumed to be positive, if the total score is 2 or more. If a patient has hypertension or a BMI higher than 30 kg/m^2^, section 3 can be considered positive. In general, if there are two or more sections with positive scores, this subject is categorized as “high risk” for OSA (obstructive sleep apnea).

Idiopathic Hypersomnia Severity Scale (IHSS) [37]: The IHSS is a self-report measure of hypersomnolence symptoms, consequences, and responsiveness to treatment. The IHSS is a 14-item self-administered questionnaire that assesses nighttime sleep symptoms and the related sleep inertia (5 items), daytime sleep symptoms and the related sleep inertia (4 items), and impaired daytime functioning due to hypersomnolence (5 items). All items are scored from 0 to 3 or 4, depending on severity, that provide a score, ranging from 0 to 50, with the highest score reflecting more severe and frequent symptoms.

Sleep Condition Indicator (SCI) [38]: The SCI is a brief 8-item tool to evaluate insomnia based on DSM 5 criteria. The SCI assesses night time and daytime symptoms and focuses both on the frequency and persistency of these symptoms. The French version of the Sleep Condition Indicator demonstrates satisfactory psychometric properties while being a useful instrument in detecting cases of insomnia disorder, consistent with features of DSM-5 [39].

##### Physical functioning

International Physical Activity Questionnaire short form (IPAQ) [40]: The IPAQ considers a 7-day recall period, identifying physical activity undertaken in the morning, afternoon, and evening. For the purposes of this research, the questionnaire was interviewer administered. Data from the IPAQ is summarized according to minutes per week of walking, minutes per week of moderate physical activity (e.g., activities that take moderate physical effort and make you breathe somewhat harder than normal such as carrying light loads, bicycling at a regular pace, or easy swimming), and minutes per week of vigorous physical activity (e.g., activities that take hard physical effort and make you breathe much harder than normal such as heavy lifting, digging, aerobics, or fast bicycling) per week. Previous research demonstrated that the IPAQ is a reliable surveillance tool to assess levels of physical activity in patients with schizophrenia [41].

##### Quality of life and general functioning

Quality of life (S-QoL) [42]: The S-QoL is a self-administered instrument to assess health-related quality of life (HRQL) among people with schizophrenia. The S-QoL, based on Calman’s approach to the subject’s point of view, is a multidimensional instrument that is sensitive to change. The scale is a 41-item questionnaire with eight subscales (psychological well-being, self-esteem, family relationships, relationships with friends, resilience, physical well-being, autonomy, and sentimental life) and a total score. The validation study showed high internal consistency reliability, reproducibility, and responsiveness. Construct validity was confirmed using established clinical and HRQL measures. The S-QoL is an efficient instrument for the measurement of the impact of schizophrenia on individuals’ lives.

Functional Remission of General Schizophrenia (FROGS) [43]: The FROGS evaluates patient functioning. It was developed using the expert consensus method following a MEDLINE and standard database search. Nineteen items were selected as gathering the core aspects of functional remission in schizophrenia detected in the literature. The FROGS was then evaluated in 432 patients with DSM-IV criteria of schizophrenia, all of them meeting the symptomatic remission criteria, total scores were shown to be highly reliable. Exploratory factor analysis after oblique rotation revealed that a three-factor solution was the most meaningful. On the basis of item content, these three factors were labeled “Social Functioning,” “Daily Life,” and “Treatment.” The FROGS total score can be used to measure a general construct for the evaluation of functional remission in schizophrenia.

Intrinsic Motivation Inventory for Schizophrenia Research (IMI-SR) [44]: Intrinsic motivation is an important mediating factor between neurocognition and psychosocial outcome. The IMI-SR is a self-report IM scale that gauges the central motivational structures identified by Self-Determinism Theory as pertinent to cognitive task engagement, skill acquisition, treatment compliance, and remediation outcome. The IMI-SR is a concise instrument, possessing good internal consistency and test-retest reliability. The final form has 21-item questionnaire comprised of 3 domains relevant to motivation for treatments (interest/enjoyment, perceived choice, value/usefulness). The IMI-SR is a viable instrument to measure intrinsic motivation in schizophrenia as part of a cognitive remediation protocol or psychosocial rehabilitation program.

All the previously mentioned measures will be implemented at baseline, 3-month, and 9-month follow-up.

##### Cognitive assessment

French National Adult Reading Test (fNART) [45]: The test consists of 40 words, graded in difficulty, whose pronunciation cannot be determined from their spelling. The ability to successfully read irregularly spelt words is relatively robust in the face of current cognitive impairment and is a sensitive marker of intellectual attainment. The fNART is a reliable and valid method of assessing premorbid intellectual ability in French speakers.

California Verbal Learning Test (CVLT) [46]: The CVLT was developed to evaluate in a multifactorial way verbal learning and memory. It has the particularity to quantify several cognitive components of verbal memory in only one test. Its duration is around 20 min. A list of 16 words (four from each of four semantic groups) is presented orally to the participants, who are required to recall the words immediately, after short and long delays and also with and without semantic cues. A recognition task is then administered. The test includes the following measures to reflect learning and recall, also called primary variables: Total Trial 1–5, Short Delay Free Recall (SDFR), Short Delay Cued Recall (SDCR), Long Delay Free Recall (LDFR), and Long Delay Cued Recall (LDCR). It also includes other variables that reflect processing of information and other cognitive processes such as Semantic Clustering and Serial Clustering, Region effects, Intrusions, and Perseverations.

Trail Making Test (TMT) [47]: Trail Making Test reflects the control of attention, visual exploration, speed, and mental flexibility. The subject is asked to connect, by making pencil lines, encircle numbers randomly arranged on a page in proper order (Part A) and encircle numbers and letters in alternating order (Part B). A French version of the normative data will be used.

##### Biological measures

The following biological measures will be taken at baseline, 3-month, and 9-month follow-up: weight, BMI, abdominal perimeter, hearth rate, and blood pressure.

Pedometer: is an electronic portable device, which counts each step a person takes by detecting the motion of the person’s hands or hips. Distance traveled (by walking or any other means) can be measured directly by a global positioning system (GPS) receiver. Our objective is to measure steps and distance covered by patients. Each patient will wear the pedometer during 1 week, 3 times during the trial: at inclusion, at 3 months just after the end of the therapy, and at 9 months just before the end of the study.
Glycemia, lipids, and C-reactive protein (CRP) will be performed with only one tube of 5 ml (dry tube)Granulocyte-macrophage colony-stimulating factor (GM-CSF), interferons (IFN)-γ, interleukins (IL)-1β, IL-2, IL-4, IL-5, IL-6, IL-8, IL-10, and tumor necrosis factors (TNF)-α: This kit is comprised of components for the measurement of human GM-CSF, IFN-γ, IL-1β, IL-2, IL-4, IL-5, IL-6, IL-8, IL-10, and TNF-α in serum, plasma, or tissue culture supernatant. They will be tested by enzyme-linked immunosorbent assays: Commercially available enzyme-linked immunosorbent assay (ELISA) kits will be used according to the manufacturers’ recommendations for measuring concentrations of intestinal fatty acid binding protein (I-FABP) (Clinisciences), soluble cluster of differentiation 14 (CD14) (Enzo), lipopolysaccharide binding protein (LBP) (Enzo), and zonulin (Servbio).

### Microbial translocation

#### DNA extraction

Plasma samples will be collected in Ethylenediaminetetraacetic acid (EDTA)-anticoagulated tubes and stored at − 80 °C. Deoxyribonucleic acid (DNA) will be extracted from 200 μL of plasma using the EZ1 DNA Tissue kit (Qiagen, Courtaboeuf, France) according to the manufacturer’s instructions. DNA will be eluted in a 100-μL final volume.

#### 16S rDNA real-time PCR

Bacterial 16S rDNA levels will be measured by polymerase chain reaction (PCR). A 20-μL amplification reaction consisted of 4 μL of LightCycler FastStart DNA Master^PLUS^ HybProbe (Roche, Meylan, France), 0.5 μmol/L forward and reverse primers, 1 μmol/L TaqMan probe, and 10 μL of the template plasma DNA. Degenerate forward (16S-F: 5′-AACAGGATTAGATACCCTGGTAG-3′ nucleotide 780 to 802) and reverse (16S-R: 5′-GGTTCTKCGCGTTGCWTC-3′ nucleotide 962 to 979) primers will be used to amplify the hypervariable region V5 of the 16S gene. Carboxyfluorescein stained probe (16S-probe: 5′-fluorescein amidites (FAM)-AACAC5TGCTCCACCGCT-BHQ1-3′ nucleotide 937 to 948, where FAM means 6-carboxyfluorescein and BHQ1 means Black Hole Quencher I) will be used as described by Kramski and colleagues [48]. The amplified region is 199 bp. The DNA is independently amplified twice in duplicate, and mean values are calculated. A negative control (molecular biology grade water) is systematically used. A standard curve is created from serial dilutions of plasmid DNA containing known copy numbers of the template. The reaction conditions for amplification of DNA are 95 °C for 10 min, followed by 45 cycles at 95 °C for 15 s, 60 °C for 60 s. The assays are performed using a LightCycler 480 II (Roche), with absolute quantification analysis performed with the Lightcycler 480 software (Roche), version 1.5, according to the manufacturer’s recommendations.

### Other data collected

#### Socio-demographic data

At inclusion, we will record age, gender, education level, marital status, occupation, living status, and income level.

#### Medical history

At inclusion, we will record age at first episode, duration of untreated psychosis, comorbid disorder including addictions, and other somatic diseases.

Current drug therapy and psychosocial interventions will be recorded at each visit.

### Biological sampling collection

We will collect blood samples:
Five milliliters on dry tube for glycemia, CRP, and lipids on dry tube1.5 ml for microbial translocation on dry tubeFive milliliters for interleukins and cytokines on dry tube

Glycemia, CRP, and lipids will be dosed in each of the 10 centers and results noted in the eCRF.

Microbial translocation analysis will be centralized in Nîmes, U1047 Inserm Unit, and interleukins and cytokines analysis will be centralized in CHU Montpellier.

Samples will be stored in each center in a − 80 °C fridge until the end of the study and sent to the analysis centers with dry-ice.

The blood samples for cytokines need to be centrifuged before freezing within 24 h from time of collection. Samples will be stored in Montpellier and preserved for 15 years.

### Participant timeline

Participants will be assessed at the beginning of the study, then re-assessed 3 months later (corresponding approximately to the end of the ENERGY intervention; if the intervention is delayed, this intermediate assessment will be performed as soon as the intervention is completed and within 15 days of the end of the intervention) and 9 months later (approximately 6 months after the intervention with a delay of 15 days maximum) for fatigue, symptomatology, global functioning, sleep, cognitive functioning, and antipsychotic medication. Blood samples will be collected at each of these assessment times (see Fig. 1).

**Fig. 1 Fig1:**
[figure not shown]
Visit schedule

### Planned trial calendar

Planned regulatory period: 6 months

Planned duration of recruitment: 36 months

Duration of participation of each subject: 9 months

Planned statistical analysis/valorization period: 6 months

Planned total trial period: 57 months

### Determination of sample size and power calculation

The main objective is to evaluate the efficacy of a therapeutic protocol for the management of fatigue in schizophrenia patients. The change in fatigue level will be compared 6 months after the intervention (9-month follow-up) between two groups of patients: one following the 3-month individual program for the management of fatigue, and one receiving care as usual. The sample size calculation is based on the change in the general fatigue score, one of the five sub-scales of the Multidimensional Fatigue Inventory (MFI) [29], measured at inclusion and 9 months later.

A study exploring the psychometric properties of the MFI in 93 out-patients with schizophrenia spectrum disorders reported a mean score on the general fatigue subscale of 13.4 (standard deviation (SD): 3.9) [30]. An earlier study reported a mean score of 16 (SD 3.2) for this sub-scale in 166 patients with fibromyalgia and chronic widespread pain [49].

In our study of SZ patients attending a day hospital, with a general fatigue subscale score greater or equal to 10 at study entry, we can expect an average score of approximately 16 (SD 4) on this subscale.

We can also hypothesize a 2-point reduction in the mean score on this sub-scale between the start of the trial and the 9-month follow-up in the group receiving the intervention. No change in the severity of fatigue is expected in the group receiving treatment as usual. Under this effect-size hypothesis, with scores in both groups set at 16 (SD 4) at inclusion, the mean score in the group receiving the intervention is expected to drop to 14. Under the hypothesis of a stable standard deviation of 4 in both groups and at both time points, power set at .085 and alpha at *p* = 0.05, 73 patients per group are necessary.

In order to allow for loses at follow-up (estimated for SZ patients at 15–20% over a 9-month period), it will be necessary to recruit 100 subjects per group.

The 9 centers participating in this study are part of the French network of expert centers in schizophrenia of the FondaMental foundation. Participants will be recruited directly from the day hospitals in each of the centers.

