### Hypotheses

The primary hypothesis is that:
Compared to the control condition (TAU), ENERGY intervention will lead to a reduction in fatigue severity (at the posttreatment and 9-month follow-up)

The secondary hypotheses are that:
2.Compared to the control condition, ENERGY intervention will lead to reductions in negative symptoms and more particularly amotivation and depression severity and will lead to increases in daily motor activity, physical functioning, quality of life, and sleep (posttreatment, 9-month follow-up).

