#### Main endpoint analysis

The efficacy of the ENERGY intervention will be studied firstly by comparing the change in fatigue score (using the scores on the MFI) between inclusion/randomization and the 9-month follow-up (primary outcome) in the intervention group compared to the TAU group.

For each subject, the relative difference (delta) between the inclusion and 9-month fatigue score will be calculated. The normality of the delta score will be tested using the Shapiro Wilk’s test. If the distribution is skewed a transformation will be performed to normalize it.

Study arms will be compared between inclusion scores and the 9-month scores using mean differences. These comparisons will be done using Student’s *T* test and general linear regression models adjusting for covariates. Socio-demographic and clinical variables will be tested as potential confounders using general linear regression models, with the *p* value set at 0.10.

A second analysis will be carried out with the general fatigue score as the outcome variable, adjusting for general fatigue score at inclusion.

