◦ General symptomatology—scores of the PANSS◦ Severity in negative symptoms—scores of the CAINS◦ Depression—scores of the CDSS◦ Risk of sleep apnea—scores on BQ◦ Hypersomnolence—scores on IHSS◦ Insomnia—scores on SCI◦ Level of physical activity—scores on IPAQ◦ Quality of life—scores on S-QoL◦ Functional remission—scores on FROGS◦ Level of intrinsic motivation—scores on IMI-SR◦ Intellectual ability—scores on fNART◦ Learning and recall—scores on CVLT◦ Attention—scores on TMT◦ Weight, BMI, abdominal perimeter, hearth rate, blood pressure◦ Number of steps and distance covered over a week using the pedometerA sub-group analysis will be performed on the intervention arm of the RCT, to identify potential factors that are linked to efficacy of the intervention. This main outcome variable will be the change in fatigue score between inclusion and the 9-month follow-up. Linear regression models will be constructed to study the effect of each dependent variable, individually and altogether in a multi-adjusted model, on the outcome.Additionally, a cross-sectional analysis of baseline data will be performed to study the biological (inflammatory markers, microbiota) and psychological factors associated with fatigue severity, overall and on each of the five MFI sub-scales, using general linear regression models.

Modifications to the initial SAP will require an amendment to the protocol. Exploratory statistical analyses not documented in the initial SAP will be discussed by the co-investigators and statisticians, in order to establish their importance and acceptability with respect to the study’s main and secondary objectives.

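### The only power statement is for the MFI general fatigue sub-scale, while the primary endpoint is an MFI score that the protocol does not identify, so the stated power is not shown to apply to it

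*Protocol article*

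**What the plan says.** All references are to the protocol article.

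- *Determination of sample size and power calculation*: "The sample size calculation is based on the change in the general fatigue score, one of the five sub-scales" of the MFI. The inputs are a mean of 16 (SD 4) at entry, a fall to 14 with the intervention, no change under TAU, and 73 evaluable patients per group, raised to 100 for losses of 15–20%.
- *Primary outcome measures*: "The primary outcome measure is the score at the Multidimensional Fatigue Inventory (MFI"). The same section says "The MFI is a self-assessment instrument with 20 items including 5 dimensions", but names neither a total nor a sub-scale. The abstract also refers only to the MFI.
- *Main endpoint analysis*: efficacy is studied first by "comparing the change in fatigue score (using the scores on the MFI) between inclusion/randomization and the 9-month follow-up (primary outcome"). It names both a t test and regression models with covariates screened at p = 0.10. It then adds: "A second analysis will be carried out with the general fatigue score as the outcome variable, adjusting for general fatigue score at inclusion".
- Under *Secondary endpoint analysis*, the baseline cross-sectional analysis looks at fatigue "overall and on each of the five MFI sub-scales", and change to 3 months is a secondary outcome.
- *Hypotheses*: the primary hypothesis is that "ENERGY intervention will lead to a reduction in fatigue severity (at the posttreatment and 9-month follow-up").
- *Inclusion criteria* set a threshold of 10 on the MFI. The sample size section places the same threshold on the general fatigue sub-scale.

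**The concern.** A power statement supports a trial only if it refers to the score that decides the trial. Here the 2-point effect and the SD of 4 are justified for general fatigue alone. The analysis section introduces general fatigue by name only after the primary comparison, which suggests that the primary comparison may use another score. A reader cannot tell whether 85% power applies to the declared endpoint.

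The choice of score is also left open in a trial where patients know their allocation and report the outcome themselves. Several MFI scores are available from one questionnaire, the main endpoint section offers more than one model, and the primary hypothesis mentions two time points. Unless the deciding score and model are fixed in advance, the choice could be made, or be seen to be made, after the results are known.

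This is more than detail left to the SAP. The protocol itself states a sizing endpoint and a primary endpoint, and the two are not shown to be the same.

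**Working it through.** **1. The plan's own figure.** Inputs from the sample size section: difference 16 − 14 = 2, SD 4, alpha 0.05. Power is printed as .085.

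- Normal approximation: n = 2 × (1.960 + 1.036)² × 4² / 2² = 71.8, so 72 per group.
- Two-sample t test with standardised effect 2/4 = 0.5: 72.8, so **73 per group**, as stated.
- By t test, one-sided testing at power 0.85 gives 59. Two-sided testing gives 64 at power 0.80 and 86 at power 0.90. Power 0.085 taken literally gives 3 (normal approximation). Of these, only two-sided 0.85 matches, so .085 is evidently a misprint.
- Losses: 73/0.85 = 85.9 (86) and 73/0.80 = 91.25 (92). Recruiting 100 covers both.
- Power for general fatigue is 85.1% at 73 evaluable per group, 88.2% at 80 and 94.0% at 100.

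The arithmetic is sound for general fatigue.

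**2. What it implies for an overall score.** The protocol gives no SD and no effect for an overall score, so the following is assumption only. Take five sub-scales, each with SD 4 and common correlation ρ. General fatigue falls by 2 points and each of the other four by a fraction f of that.

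- SD of the sum = 4 × √(5 + 20ρ)
- Difference in the sum = 2 + 8f

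Power at 73 per group (two-sided t test):

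| ρ | SD of sum | f = 0 | f = 0.25 | f = 0.5 | f = 0.75 | f = 1 |
|---|---|---|---|---|---|---|
| 0.3 | 13.27 | 14.8% | 44.0% | 77.5% | 95.1% | 99.5% |
| 0.5 | 15.49 | 12.1% | 34.1% | 64.2% | 87.3% | 97.2% |
| 0.7 | 17.44 | 10.6% | 28.0% | 54.2% | 78.6% | 93.1% |

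The range is about 11% to over 99%. At f = 0.5, 85% power would need 89 (ρ = 0.3), 121 (ρ = 0.5) or 153 (ρ = 0.7) per group. The stated 85% says nothing definite about an overall score in either direction.

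**3. Type I error, if either of two scores could count.** Suppose a significant result at 0.05 on either the overall score or general fatigue at 9 months were accepted. The correlation between the two is (1 + 4ρ)/√(5 + 20ρ), which is 0.66, 0.77, 0.87 and 0.96 for ρ = 0.3, 0.5, 0.7 and 0.9. The bivariate normal probability of at least one false positive is then 8.5%, 8.0%, 7.3% and 6.3%.

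**4. The model matters as well as the score.** On one score with baseline-to-9-month correlation r, the change-score test and the baseline-adjusted test have correlation √((1 + r)/2). At r = 0.5 this is 0.87, and accepting either gives 7.3%. Naming a score without naming a model leaves this open.

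The model also affects power. The SD of the change is 4 × √(2(1 − r)), which equals 4 only if r = 0.5. At r = 0.3 it is 4.73, and change-score power at 73 falls to 72%. The residual SD of the baseline-adjusted model is 4 × √(1 − r²), which never exceeds 4. Its power at 73 is 88% at r = 0.3 and 93% at r = 0.5. The protocol does not state r.

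**The case against.** The strongest reply is that the main endpoint section may describe one score analysed in two ways: first the change in general fatigue, then its 9-month value adjusted for baseline. The entry threshold supports this, since the protocol expresses the same cut-off of 10 once on the MFI and once on the sub-scale, so the authors do sometimes use the instrument's name for the sub-scale. On this reading the 85% does belong to the primary endpoint. The separation of overall fatigue from the sub-scales occurs only in a baseline cross-sectional analysis and does not settle which score the primary comparison uses. This reading is possible, but the text does not state it, and naming general fatigue only for the later analysis points the other way. The endpoint remains unidentified.

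A reader might infer that success can be claimed by several routes and that type I error is inflated. The protocol does not support that. It sets an order, with a first analysis labelled primary and then a second, and nowhere lets a second result or the 3-month result rescue the first. It also does not say which result decides, so the error rates in the working are conditional only.

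A reader might also infer that the trial is underpowered. That is not shown either. The 11% figure needs an intervention that moves general fatigue alone, whereas Table 1 targets physical and mental fatigue as well. If all five sub-scales fall by 2 points, power for the overall score is 93% or more under the same assumptions.

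The time-point discrepancy is minor. The abstract, primary objective, sample size section and main endpoint analysis all point to 9 months, and 3 months is secondary. The hypothesis reads like a wording slip.

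**Conclusion.** The point holds in a limited form. The protocol's one power statement (73 per group, about 85% with .085 read as 0.85) is for general fatigue, and the primary endpoint is an MFI score that is never identified. The power is therefore not shown to apply to the endpoint that decides the trial.

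If general fatigue is meant, nothing is lost and 73 stands, provided the SD of 4 suits the chosen model. If an overall score is meant, its power cannot be computed from the document. The range of about 11% to over 99% rests on assumed equal sub-scale SDs of 4, correlations of 0.3 to 0.7, and other sub-scales moving between none and all of the general fatigue effect.

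A type I error of about 6–8.5% for two scores at 9 months would arise only if either result were allowed to count, which the protocol neither states nor excludes. The correction should be made before any outcome data are seen, because it settles what the trial can claim.

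**What to change.** 1. In the abstract, *Primary outcome measures* and *Main endpoint analysis*, name the MFI general fatigue sub-scale at 9 months as the single primary endpoint. This keeps 73 evaluable and 100 recruited per group. Make the overall score and the other four sub-scales secondary.
2. If the sponsor prefers the overall score, restate the power with that score's own SD and expected effect, and revise the sample size if needed.
3. Name one deciding model, tested two-sided at 0.05. The 9-month score adjusted for its baseline value is a natural choice: the main endpoint section already plans it for general fatigue, and with SD 4 it gives at least 85% power at 73 per group whatever the baseline correlation. List the change-score t test and the regression with screened covariates as sensitivity analyses.
4. Remove the posttreatment assessment from the primary hypothesis and keep 3 months as secondary.
5. Correct the printed power of .085, and reconcile the entry-score wording of the inclusion criteria with that of the sample size section.

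The cost is a wording amendment to the protocol, carried into the SAP. No new data are needed, because every MFI score comes from the same questionnaire. Only option 2 could change the sample size.
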